## Abstract

**Background:**

Childhood undernutrition is a major public health concern that needs special attention to achieve 2025 global nutrition targets. Moderate acute malnutrition (MAM), manifest as wasting (low weight-for-height), affects 33 million children under 5, yet there are currently no global guidelines for its treatment. We recently performed a randomized-controlled clinical study of a microbiota-directed complementary food formulation (MDCF-2) in 12-18-month-old Bangladeshi children with MAM. The results revealed that MDCF-2, freshly prepared each day, produced a significantly greater improvement in ponderal growth than a standard ready-to-use supplementary food (RUSF), an effect that is associated with repair of the disrupted gut microbial community development that occurs in children with MAM. To test the generalizability of these results in acutely malnourished children at other sites, there is a pressing need for a packaged, shelf-stable, organoleptically-acceptable formulation that is bioequivalent to MDCF-2. This report describes the protocol for a clinical study to evaluate candidate formulations designed to meet these criteria.

**Methods:**

A randomized single-blind study will be conducted in 8-12-month-old Bangladeshi children with MAM to compare the efficacy of alternative shelf-stable MDCF prototypes versus the current MDCF-2 formulation that is produced fresh each day. V4-16S rDNA amplicon and shotgun sequencing datasets will be generated from faecal DNA samples collected from each child enrolled in each group prior to, during, and after treatment to determine the abundances of MDCF-2-responsive bacterial taxa. Efficacy will be assessed by quantifying the change in representation of MDCF-2-responsive gut bacterial taxa after 4-weeks of treatment with freshly prepared MDCF-2 compared to their changes in abundance after treatment with the prototype MDCFs. Equivalence will be defined as the absence of a statistically significant difference, after 4-weeks of treatment, in the representation of faecal bacterial taxa associated with the response to MDCF-2 in participants receiving a test MDCF.

**Discussion:**

This trial aims to establish acceptability and equivalence with respect to microbiota repair, of scalable, shelf-stable formulations of MDCF-2 in 8-12-month-old Bangladeshi children with moderate acute malnutrition.

**Trial registration:**

ClinicalTrials.gov (NCT05094024). The trial has been registered before starting enrolment on 23 October 2021.

## Background

Worldwide, 47 million children under 5-years-of-age are acutely malnourished (wasted), while 149 million are short for their age (stunted) [1, 2]. In Bangladesh, the prevalence of stunting, underweight and wasting among children under 5 were 31%, 22% and 8%, respectively [3]. However, the prevalence of different forms of childhood malnutrition, especially acute malnutrition, is likely to increase as millions of children in low- and middle-income countries around the world are experiencing acute hunger and food insecurity as a result of the ongoing Covid-19 pandemic and related economic turbulence [4]. Moderate acute malnutrition (MAM) in children is defined by anthropometry based on the WHO criteria [(i.e., weight-for-height (WHZ) between 2 and 3 standard deviations below the median of the WHO Child Growth Standards) and/or upper mid-upper-arm- circumference (MUAC) between 115mm and 125mm] [5]. There are currently no global guidelines for the treatment for MAM. Therefore, there is a great need for effective nutritional interventions that could be used to treat undernutrition in infants/children and simultaneously facilitate progress towards achieving the WHO global nutrition targets set for 2025 [6].

Our recent work in undernourished Bangladeshi children has focused on the contribution of the gut microbiota to their nutritional status. Using culture-independent methods to analyze serially collected faecal samples collected from healthy children and from those with MAM, we found that MAM is associated with impaired microbiota development (microbiota ‘immaturity’) [7, 8]. We showed that this immaturity is not repaired by standard nutritional interventions [7, 8]. Furthermore, preclinical studies using gnotobiotic animal models disclosed that colonization with gut communities from undernourished children transmitted impaired weight gain and bone growth phenotypes, plus immune and metabolic abnormalities [9]. Based on these observations, gnotobiotic mice and gnotobiotic piglets were used to screen combinations of culturally acceptable food staples that are commonly consumed as complementary foods in Bangladesh for their ability to increase the fitness of bacterial taxa underrepresented in the immature microbiota of acutely malnourished children. This effort led to the development of several microbiota-directed complementary food (MDCF) prototypes [8, 10]. Three of these formulations were compared to an existing ready-to-use supplementary food (RUSF) in a 1-month randomized controlled ‘pre-POC’ study in 12-18-month-old children with MAM living in an urban slum in the Mirpur area of Dhaka, Bangladesh [8, 10]. One of these formulations (MDCF-2) ‘repaired’ the gut microbial community to state similar to that found in aged-matched healthy Mirpur children, and altered the abundances of plasma proteins in directions that were indicative of improved growth/health status.

We subsequently performed a larger, longer proof-of-concept (POC) study to compare the effects of MDCF-2 and RUSF on the growth of 12-18-month old children with MAM. Despite its lower caloric density (4.30 versus 4.96 kcal/g), children who received MDCF-2 exhibited a significantly faster rate of weight gain during the 3-month period of intervention compared to those consuming RUSF. This improvement was associated with an increase in the abundance of the underrepresented bacterial taxa that MDCF-2 was designed to promote [11].

Both the pre-POC and POC studies described above used a formulation of MDCF-2 that was prepared fresh each day at icddr,b facilities. The objective of the current study is to test industrially manufactured, packaged, shelf-stable formulations of MDCF that would greatly facilitate the expansion of tests of its efficacy to other sites/populations. These studies require development of a uniform formulation that satisfies the following criteria: (i) biological activity equivalent to the current freshly prepared formulation of MDCF-2; (ii) shelf-stable, free of microbial contamination, with satisfactory organoleptic properties; (iii) conforms to existing WHO/UNICEF specifications for a nutritional intervention for treating MAM; (iv) can be produced at scale using ingredients from sustainable sources at an affordable price with the potential for distribution across national boundaries. Here, we present the research protocol for a pre-POC study of candidate shelf-stable MDCF prototypes in Mirpur area of Dhaka city, Bangladesh.

## Methods

### Goal and objectives

The primary goal of the trial is to compare the efficacy of a shelf-stable formulation of MDCF-2 with that of freshly prepared MDCF-2 and assess its organoleptic acceptability. We will also test the extent to which alternative MDCF formulations are able to repair the gut microbiota of children with MAM compared to the repair produced by the current MDCF-2 formulation.

### Study design

Figure 1 describes the design of this randomized single-blind pre-POC trial that was approved by the Ethical Research Committee at the icddr,b on 28 June 2021 (PR- 21019).

**Fig. 1 Fig1:**
[figure not shown]
Study design

It will be conducted in three phases. The first 2 weeks after enrolment are a ‘run-in’ phase where children are followed on their normal diets, without nutritional intervention. During this phase, collection of fecal samples will allow the baseline configuration of their microbiota to be characterized prior to treatment. Subsequently, participants will be randomized to receive one of the food prototypes, administered under supervision, twice daily for 4 weeks. Fecal samples collected at the end of the intervention phase will be used to assess the extent of microbiota repair produced by each treatment. After completion of the intervention, each child will be followed for another 2 weeks. Fecal samples collected during this phase will be used to assess the durability of the microbiota repair. Blood samples will be collected at baseline and at the end of the treatment phase to quantify levels of plasma protein biomarkers/effectors of healthy growth [11].

Eligible participants are 8-12-month-old Bangladeshi children with MAM. The study will be conducted among members of the slum population in Baoniabad of Mirpur, one of the 21 administrative units of the nation’s capital, Dhaka. Mirpur was selected because it is inhabited by poor and lower middle-class families, and because residential and sanitary conditions are typical of congested urban settlements. Additionally, the investigators have established several field sites in this area and have ongoing research activities in the community.

### Screening, consent & enrolment of study participants

A trained Field Research Assistant (FRA) will explain the study design and methodology in detail, describe potential risks and benefits, answer any questions from the parent(s), and invite the parent(s) to enroll their child in the study. If the parent(s) are interested, they will proceed to screening and consenting. Eligibility will be determined based on the inclusion and exclusion criteria listed in Table 1.

**Table 1 Tab1:** Inclusion/exclusion criteria of the study participants

**Inclusion** Parent(s) willing to sign consent form Child aged 8–12 months WLZ score < -2 to -3 without bilateral pedal edema at the time of randomization Parent(s) willing to bring the child to the feeding centre according to the pre-defined schedule **Exclusion** Meeting any of the following criteria will exclude a subject from study participation – Medical conditions: Malnourished children with complications requiring acute phase treatment in a hospital, children with tuberculosis (diagnosis based on WHO 2014 guidelines which have been incorporated in the national TB control guidelines of Bangladesh). The guidelines depend upon the following five diagnostic principles (three out of five should be positive): • Specific symptoms of TB • Specific signs of TB • Chest X-ray • Mantoux test • History of contact Any congenital/acquired disorder affecting growth, i.e., known case of trisomy-21 or cerebral palsy; children on an exclusion diet for the treatment of persistent diarrhea; having known history of soy, peanut or milk protein allergy Severe anemia (< 8 mg/dl) Antibiotic use (within last 15 days before the onset of intervention) Ongoing maternal antibiotic usage for breastfeeding infants Receiving concurrent treatment for another condition	

If a subject is eligible to participate, the consent process will consist of a thorough review of the written consent form in a manner appropriate for the parents’ literacy level. Prior to parental signing of the consent form, the child will undergo thorough clinical examination by study physician. In addition, there may be a recommendation that a child undergo laboratory tests to exclude any organic diseases or any other causes of secondary malnutrition. During this period, parents of the participants will have an opportunity to ask any questions about the study. If the FRA determines that participants have demonstrated adequate comprehension of the study, the consent form will be signed by the FRA and the child’s parent(s). If the parent(s) are not sufficiently literate to read and/or sign the consent form, consenting and a thumbprint signature will be obtained in the presence of a witness who is not associated with the study. The child’s parent(s) will be provided with a copy of the signed consent form.

At the beginning of the study, information will be collected on the demographic characteristics of the participants (family income, standard/type of housing, family structure, parental education, etc.). FRAs will collect anthropometry data by recording the child's weight using a digital scale with 2g precision (Seca, model 728, Germany), length (Seca model 416 infantometer), and mid-upper arm circumference (MUAC) to the nearest millimeter (using a non-stretch tape). Z scores will be calculated using the new child growth standards of the World Health Organization [12]. Collection of anthropometric data will occur at weekly intervals throughout the study.

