### Intervention arms

The trial will have 5-arms designed to compare the efficacy of alternative MDCF formulations in repairing the gut microbiota of children with MAM compared to the repair produced by the current kitchen prepared MDCF-2 formulation. All the formulations are fortified with equal amount of vitamins and minerals. Children will be randomly assigned to one of the interventions after enrolment.Arm 1 - Reference control: kitchen-prepared MDCF-2Arm 2 - Individually packaged, pre-measured sachets of MDCF-2 ingredients, combined and reconstituted in the home setting prior to consumptionArm 3 - MDCF-2 shelf-stable foil pouch formulation with green banana powderArm 4 - MDCF shelf-stable foil pouch formulation with sweet potato instead of green bananaArm 5 - Ready-to-use supplementary food (RUSF)

Table 2 provides an overview of the interventions.

**Table 2 Tab2:** Arms and Interventions

	Arms	Intervention
1	Active Comparator: Central kitchen-prepared MDCF-2. Children randomized to this arm will receive 25g of kitchen-prepared version of MDCF-2 twice daily.	Dietary Supplement: Central kitchen-prepared version of MDCF-2. Kitchen-prepared MDCF-2 containing chickpea flour, peanut flour, soybean flour, green banana pulp, sugar, soybean oil and micronutrient mix. This version of MDCF-2 will be freshly prepared in a central kitchen on a daily basis and provided to participants on the same day.
2	Experimental: ‘Jump-start’ version of MDCF-2. Freshly reconstituted MDCF-2 ingredients. Children randomized to this arm will receive individually packaged MDCF-2 ingredients, combined into 21.7 g servings provided twice daily.	Dietary Supplement: Jump-start version of MDCF-2. Freshly reconstituted MDCF-2 ingredients. This version of MDCF-2 is comprised of its individually packaged ingredients. Separate premeasured sachets of chickpea flour, peanut paste, soybean flour, green banana powder, sugar, soybean oil and micronutrient mix will be combined and reconstituted prior to each feeding session.

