3	Experimental: MDCF-2 shelf-stable foil pouch prototype with green banana powder. Children randomized to this arm will receive 25g of the shelf-stable foil pouch prototype with green banana powder twice daily.	Dietary Supplement: MDCF-2 shelf-stable foil pouch prototype with green banana powder. This shelf-stable foil pouch prototype of MDCF-2 contains chickpea flour, peanut flour, soybean flour, green banana powder, sugar, soybean oil and micronutrient mix, prepared by an industry partner following the formulation developed at icddr,b.
4	Experimental: MDCF-2 shelf-stable foil pouch prototype with sweet potato. Children randomized to this arm will receive 23.3g of this MDCF prototype with sweet potato twice daily.	Dietary Supplement: MDCF-2 shelf-stable foil pouch prototype with sweet potato. This shelf-stable MDCF prototype contains chickpea flour, peanut flour, soybean flour, sweet potato, sugar, soybean oil and micronutrient mix. This version of MDCF-2 will be prepared by an industry partner following the formulation developed at icddr,b.
5	Experimental: Ready-to-use supplementary food (RUSF). Children randomized to this arm will receive 25g RUSF twice daily.	Dietary Supplement: Ready-to-use supplementary food (RUSF) arm. Locally-produced ready-to-use supplementary food (RUSF) is used as part of a nutritional program to treat moderate acute malnutrition in children over 6 months-of-age. RUSF is eaten directly from the package with no dilution, mixing or cooking. RUSF contains rice, lentil, powdered low-fat milk, soybean oil, sugar, and micronutrient mix.

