### Monitoring food consumption and collection of meta-data

Each child will be offered approximately 25 grams of the diet in each feeding session (Table 2). Feeding will take place under the direct supervision of trained study personnel. The intervention diets are pre-weighed. Mothers will be instructed to collect all unconsumed food for weigh-back so that the amount consumed by each child can be calculated. Only water from the mug is allowed to drunk; the amount of water consumed is also measured. The quantity of MDCF or RUSF consumed will be monitored and calculated in every feeding session. Multiple food frequency data and 24 hours dietary recall data will also be collected.

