### Sample size

The sample size was informed by the faecal 16S rRNA gene amplicon datasets generated for the proof-of-concept study of 12 to 18-month-old Bangladeshi children with MAM.^11^ In that study, we identified 209 bacterial Amplicon Sequence Variants (ASVs) that were present above 5 counts in at least 5% of the 939 faecal samples analyzed from 118 participants. We calculated 95% confidence intervals (CI; mean ± 1.96 standard error) for the change (delta) in abundance of each of the 209 ASVs between day 0 (pre-intervention) and 4 weeks of intervention for the 59 children in the MDCF-2 treatment group of the POC study. Using a bootstrapping approach with ASV data from 5000 subsets of 20 children from the MDCF-2 group and 5000 subsets of 20 children from the RUSF group, we identified 121 ASVs whose mean changes in abundance for the MDCF-2 subsets fell within the 95% CI of the mean changes for the 59 MDCF-2 participants, but not in children who had received RUSF, with 80% power (“MDCF-2-responsive ASVs”). Therefore, each arm will include a minimum of 20 children who complete the study. Considering potential drop-outs (15%), 23 children will be recruited per arm.

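### The allergy exclusion names soy, peanut and milk protein but leaves out other study-food ingredients, notably chickpea (Arms 1–4) and lentil (Arm 5)

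*Protocol article*

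**What the plan says.** The section on screening, consent and enrolment fixes the rule: "Eligibility will be determined based on the inclusion and exclusion criteria listed in Table 1". Within Table 1, food allergy appears once, as "having known history of soy, peanut or milk protein allergy". The list is closed: it has no wording for other ingredients, and the table contains no criterion based on investigator judgement.

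The section on intervention arms states that "Children will be randomly assigned to one of the interventions after enrolment". Table 2 then gives the ingredients. For Arm 1 it reads "Kitchen-prepared MDCF-2 containing chickpea flour, peanut flour, soybean flour, green banana pulp, sugar, soybean oil and micronutrient mix"; Arms 2, 3 and 4 also contain chickpea flour. For Arm 5 it reads "RUSF contains rice, lentil, powdered low-fat milk, soybean oil, sugar, and micronutrient mix".

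Two other provisions bear on the point. At screening, "Prior to parental signing of the consent form, the child will undergo thorough clinical examination by study physician". During the intervention, "Feeding will take place under the direct supervision of trained study personnel".

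**The concern.** The sponsor has accepted that a known allergy to a study food is a reason not to enrol, but Table 1 applies this to only part of the ingredient list in Table 2. Chickpea is the first-listed ingredient of all four MDCF foods, and lentil is in the RUSF. As written, a child with a known allergy to one of these is eligible, and no allocation rule steers that child away from the food.

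What is at stake is the safety of an individual infant. The children are 8 to 12 months old with moderate acute malnutrition, and the assigned food is given twice daily for 4 weeks, or 2 × 28 = 56 servings. The statistical conclusions are not at stake: chickpea is in the reference food and in every test MDCF, and lentil is only in the RUSF.

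**Working it through.** **Ingredients against the exclusion.** Setting Table 2 beside Table 1:

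| Ingredient | Arms | Covered by Table 1? |
|---|---|---|
| Soy (flour and/or oil) | 1–5 | Yes |
| Peanut | 1–4 | Yes |
| Milk | 5 | Yes |
| Chickpea | 1–4 | No |
| Lentil | 5 | No |
| Rice | 5 | No |
| Green banana | 1–3 | No |
| Sweet potato | 4 | No |

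**Other criteria that might close the gap.** The exclusion-diet criterion is limited to diets for persistent diarrhoea. The criterion on concurrent treatment for another condition does not clearly reach an allergy managed by avoidance alone. The criterion on complications needing hospital treatment does not apply.

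**Chance of being assigned the food.** The Sample size section gives "Considering potential drop-outs (15%), 23 children will be recruited per arm", and there are five arms. Taking allocation as equal:

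- Places: 5 × 23 = 115.
- Chickpea foods: 4 × 23 = 92, and 92/115 = 80%.
- Lentil food: 23, and 23/115 = 20%.

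**Expected number of children.** The article gives no prevalence. For illustration, assume that 0.1% to 1% of enrolled children have a known allergy to the food in question:

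- Enrolled, per food: 115 × 0.001 = 0.115 to 115 × 0.01 = 1.15.
- Assigned chickpea: 0.8 × 0.115 = 0.09 to 0.8 × 1.15 = 0.92.
- Assigned lentil: 0.2 × 0.115 = 0.02 to 0.2 × 1.15 = 0.23.

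**Effect on arm size.** One withdrawal is 1/23 = 4.3% of an arm. The allowance is 23 − 20 = 3 children, so a single case is absorbed.

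**The case against.** The strongest reply is that the concern covers only an allergy the family already knows about, and that such a family has several chances to mention it. Staff explain the study and its risks, a physician examines the child, parents can ask questions before signing, a two-week run-in without study food comes first, and feeding is then supervised. For harm to occur, a parent who knows of the allergy would have to say nothing at each step. That makes a case unlikely, and this part of the reply stands. But none of these steps is an allergy rule. An examination need not reveal a known allergy unless the history is asked for, and supervision during feeding acts only once the food is being given.

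It can also be said that a condensed article leaves screening detail to the full protocol, and that naming particular allergens is a legitimate choice. The fuller document may indeed be worded more widely. Here, though, the article prints the criterion itself, and that criterion does not match the article's own ingredient table.

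A third reply is that the prevalence range has no source in the article, and that applying it unchanged to enrolled children ignores refusals and detection at screening. That is fair. The counts above are best read as illustrative upper figures under each assumed prevalence.

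**Conclusion.** The point holds as a minor one. Table 1 does not exclude a known allergy to chickpea, lentil, rice, green banana or sweet potato, all of which are study-food ingredients. A child with known chickpea allergy who was enrolled would have a 4 in 5 chance of being assigned a chickpea food; for lentil the chance is 1 in 5. Both figures rest on equal allocation. Under the assumed 0.1% to 1% prevalence, fewer than one child would be expected to be assigned either food, and quite possibly none. Sample size, power and the primary equivalence analysis are unaffected. The case for acting is that a foreseeable risk to an infant can be removed at very little cost.

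**What to change.** In Table 1, replace the three named allergies with: known allergy to any ingredient of any study food, confirmed with the parent before randomisation. This needs no new test, since it widens a history question already required for soy, peanut and milk. It also covers the remaining unlisted ingredients and stays correct if a formulation changes.

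The text change is one line. The trial already had ethics approval (28 June 2021) and began enrolling on 31 October 2021, so a change during recruitment would ordinarily mean a minor eligibility amendment and an updated screening form. Under the assumed range, about 0 to 1 further children per 115 would be excluded for each of chickpea and lentil.

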### Collection, preparation and archiving of biological samples

All biological samples (blood and faeces) will be collected according to the standard operating procedures (SOPs) described in our previous publications [11]. Five millimeters of blood will be collected from each participant before and after the treatment phase (Fig. 1). Whole blood samples will be centrifuged at 3000 x g for 10 minutes to separate the plasma [14]. Aliquots of plasma sample will be stored at -80 °C until analysis.

Faecal samples will be collected weekly during the run-in, treatment and wash-out phases of the study. At the site of collection, samples will be aliquoted into sterile, pre-labelled 2 mL cryovials and immediately placed into pre-charged liquid nitrogen dry cryo-shippers (within 20 minutes of their production by trial participants) for transport back to the laboratory. At the laboratory, vials will be placed on dry ice while they are organized and subsequently transferred to 9x9 freezer boxes. These boxes will be maintained in a -80^o^C freezer prior to analysis. No additives, preservatives or media will be added to the faecal samples.

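### Table 1 prints the severe-anaemia exclusion in mg/dl with no analyte named; read literally as haemoglobin, the numeric limit excludes no child, and nothing else in the article corrects it

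*Protocol article*

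**What the plan says.** The section on screening, consent and enrolment makes Table 1 the working rule: "Eligibility will be determined based on the inclusion and exclusion criteria listed in Table 1". Within the table, the exclusions act singly: "Meeting any of the following criteria will exclude a subject from study participation". One of them is "Severe anemia (< 8 mg/dl", with the bracket closing straight after the unit. The analyte is not stated, and the limit is not repeated anywhere else in the article.

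Two other provisions come near the same ground. Another Table 1 exclusion covers "Malnourished children with complications requiring acute phase treatment in a hospital". The text after the table requires a physician's examination before the consent form is signed and adds that "there may be a recommendation that a child undergo laboratory tests to exclude any organic diseases or any other causes of secondary malnutrition". Neither gives a limit for anaemia.

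The section on biological samples says that "blood will be collected from each participant before and after the treatment phase", so every enrolled child is due two research blood draws.

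**The concern.** A numeric limit in an eligibility table is a decision rule: a screener compares a laboratory value with it and includes or excludes the child. Haemoglobin concentrations are of the order of grams per decilitre, that is, thousands of milligrams per decilitre. A limit of 8 in mg/dl therefore cannot separate severely anaemic children from others.

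Two things depend on the true limit. First, the children are 8 to 12 months old and have blood taken twice, so whether severe anaemia excludes a child matters to them. The article gives no reason for the criterion, so linking it to the blood draws is an inference. Second, anyone who wants to repeat the trial or judge to whom its results apply needs to know the limit, and cannot recover it from this article.

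**Working it through.** There is no design figure to reproduce here. The check is a unit conversion and a search for any text that would correct the printed limit.

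**Inputs**
- Printed limit: below 8 mg/dl (Table 1, exclusions).
- Analyte: not named. Haemoglobin is assumed.
- Haemoglobin values: the article gives none. A deliberately wide range of 1 to 11 g/dl is assumed.

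**Step 1: convert the printed limit.** With 1 g = 1000 mg, 8 mg/dl ÷ 1000 = 0.008 g/dl. With 10 dl in a litre, 0.008 × 10 = 0.08 g/L.

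**Step 2: compare haemoglobin values with the limit.** Value in mg/dl = value in g/dl × 1000; ratio to the limit = value in mg/dl ÷ 8.

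| Assumed haemoglobin (g/dl) | In mg/dl | Ratio to 8 mg/dl | Below the printed limit? |
|---|---|---|---|
| 1 | 1000 | 125 | No |
| 2 | 2000 | 250 | No |
| 3 | 3000 | 375 | No |
| 5 | 5000 | 625 | No |
| 8 | 8000 | 1000 | No |
| 11 | 11000 | 1375 | No |

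Even the lowest assumed value is 125 times the limit, so the result does not depend on where in the range a child lies.

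**Step 3: look for a correction elsewhere.**
- The limit occurs once. No other section restates it in another unit, names the analyte or defines severe anaemia.
- The exclusion for complications needing acute hospital treatment overlaps only where anaemia leads to such treatment, and it carries no haemoglobin limit.
- Laboratory tests at screening are only something that may be recommended, again with no anaemia limit.

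None of these restores a usable number.

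**Step 4: see what else in the plan uses the limit.** The sample size section, the primary outcome and the equivalence rule in the analysis plan do not refer to it. The consequence is confined to eligibility.

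**The case against.** The strongest reply is that the error announces itself. The criterion is severe anaemia, and the figure is a gloss in brackets. A clinician who reads it as haemoglobin sees at once that the unit is impossible, falls back on the words, and also has the physician's examination to rely on. A plausible but wrong number would be more dangerous. The sample-collection section contains a similar slip, giving a blood volume in millimetres, which fits loose unit editing in the article at least as well as a defective rule in the trial.

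Much of this stands. It rules out three stronger readings that a reader might infer:

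- **That the exclusion never operates in the trial.** The arithmetic shows this only for the literal number. The words and the examination remain, and trained staff may well have applied the intended limit.
- **That children were screened against this unit.** Ethics approval is dated 28 June 2021 and enrolment began on 31 October 2021, while the article describes recruitment as under way. It was therefore written after screening had started. Children enrolled before then were presumably screened from the approved protocol and its forms, which are not shown.
- **That the enrolled population differs from the intended one.** The article offers no evidence of this. It gives no anaemia prevalence either, so the number of children who might be affected cannot be estimated.

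The reply does not remove the point itself. Recognising that a unit is impossible does not tell the reader what the approved limit is, and the article supplies it nowhere else. Nor is this detail that an article may leave to the full protocol: a figure is stated, and stated in a unit that cannot work.

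**Conclusion.** The point holds as an error in a stated eligibility threshold. Read as haemoglobin, the printed limit is 0.008 g/dl; every value in the assumed range of 1 to 11 g/dl exceeds it at least 125-fold, so the number taken literally excludes no child. This rests on two assumptions: that the analyte is haemoglobin, which the article does not say but which is the only natural reading, and that haemoglobin lies in the wide range used.

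It is very probably a unit slip. Whether it is confined to the article or also sits in the approved protocol or the screening form cannot be told from the document. The point supports a correction and a check of those two sources. It does not support a finding that any severely anaemic child was enrolled, and it has no bearing on the sample size, the primary outcome or the analysis.

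**What to change.** 1. In Table 1, name the analyte, and reconcile the threshold and its unit with the ethics-approved protocol and the screening form. The investigator should confirm the result. No cut-off is proposed here.
2. Only if the approved protocol or the form turns out to carry the same unit: correct it there, and re-check the screening records of children already enrolled against the confirmed criterion.

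The first step costs one line in the article and a comparison of two existing documents. As enrolment was expected to run to 31 December 2022, an early check would also serve children not yet screened. The second step, if it is needed, uses records already held and calls for no new data.
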